### Outcomes

The primary outcome is the difference in the change in glycated hemoglobin level between intervention and control groups after 6 months. Secondary outcomes include changes between groups in fasting blood glucose, total cholesterol, low-density lipoprotein cholesterol, high-density lipoprotein cholesterol, triglycerides, systolic and diastolic blood pressure, body mass index, waist circumference, fat-free mass, and fat mass.

Secondary outcomes also include the incidence of exercise-related injuries and adverse events, as well as the cost-utility of the walking football exercise program.

### Assignment of Interventions

The principal investigator will use a computerized random number generator to randomize participants.

Each patient will have a unique patient study number, which will be given immediately by the randomization software (the latest version of Excel Office 365).

Family medicine doctors at each PHCU will invite patients for an appointment; then, family medicine doctors will provide information about the study, assess the availability for participation, and collect informed written consent. After consent, the participants will be invited to perform a treadmill cardiac stress test.

If still eligible after the stress test, the participants will be enrolled in the study by the research team, who will provide an opaque envelope with the codification previously generated for each participant; the participant will then open the envelope and check his allocation for the intervention or control group.

Blinding of the participants, health care professionals, and research team members will not be possible.

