### Design

This study is based on a parallel-group, randomized controlled trial with a 6-month duration. Eligible participants will be randomized using a 1:1 ratio within each primary health care unit (PHCU) to intervention or control groups. The intervention will consist of a 60-minute walking football exercise program, 3 times per week (nonconsecutive days), for 24 weeks. The control group will maintain daily life routines and continue with usual care. The study design is represented in Figure 1.

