#### Exclusion Criteria

Individuals with issues identified in the cardiac stress test, namely asymptomatic cardiac or hemodynamic problems, will be excluded from the study.

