### Intervention and Control Groups

Participants assigned to the intervention group will enroll in a walking football exercise program and receive basic sports material (eg, sports bag, t-shirt, and sports shoes). The participants will be organized into 5 groups of 20 players in different time schedules. Each group will have 60-minute walking football exercise sessions, 3 times per week (nonconsecutive days), for 24 weeks (72 sessions).

Walking football sessions will be conducted on a football field and supervised by a football coach certified by the Union of European Football Associations and by a nurse.

The sessions will consist of strength and conditioning exercises, technical skill drills, and small-sided and conditioned walking football games, including warm-up and cool-down periods.

The participants from the intervention and control groups will be asked to maintain daily life routines (lifestyle-related physical activity and dietary pattern) and continue with usual care (diabetes consultations and pharmacological regimen). In Portugal, the usual care at a PHCU already includes brief counseling for physical activity and sedentary behavior [25].

Participants from the control group will also receive basic sports material (eg, sports bag, t-shirt, and sports shoes).

All activities, participation rules, project team members, and the sports facilities will be presented to participants and their families before starting the intervention.

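### The principal investigator generates the allocation codes and belongs to the unblinded team that enrols, so a man's arm can be known before he enters the trial

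*Protocol article*

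**What the plan says.** All of the following is in the protocol article.

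- **Who generates.** Assignment of Interventions: "The principal investigator will use a computerized random number generator to randomize participants". The software named is Excel, which issues each study number at once; the article does not say what event triggers it.
- **Who enrols.** Same section: "If still eligible after the stress test, the participants will be enrolled in the study by the research team".
- **Who delivers the allocation, and what it is.** The sentence continues with that team handing over the envelope: "the research team, who will provide an opaque envelope with the codification previously generated for each participant". Then "the participant will then open the envelope and check his allocation for the intervention or control group".
- **Who is on the team.** Data Collection (text after Table 2) has the principal investigator train the other members of the research team, so the principal investigator is one of them. Assignment of Interventions says that research team members cannot be blinded.
- **Who is randomized.** Design: "Eligible participants will be randomized using a 1:1 ratio within each primary health care unit (PHCU) to intervention or control groups".
- **The last gate.** Exclusion Criteria: "Individuals with issues identified in the cardiac stress test, namely asymptomatic cardiac or hemodynamic problems, will be excluded from the study".
- **What is said about bias.** Limitations relies on the objectivity of glycated hemoglobin to soften the lack of blinding. It does not discuss concealment of the allocation.

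**The concern.** Allocation concealment requires that nobody who can influence whether a man enters the trial knows the arm he would receive. Here one team generates the codes, admits the man and delivers the result, and no separation of these roles is described. The code is attached to a participant and is not described as the next slot in a sequence, so the person who made the list could look up a particular man.

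If that knowledge affects who is enrolled, the arms differ at baseline in ways that need not be measured. Intention-to-treat analysis keeps men in their assigned arms but does not repair a selected intake, and covariate adjustment reaches only what was recorded. HbA1c being a laboratory value does not help either: it limits bias in measuring the outcome, not in choosing who is measured.

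**Working it through.** The main point involves no arithmetic; it follows from the order of steps and the roles. One side question, balance, can be checked numerically.

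**1. Order of steps in Assignment of Interventions.** Family doctor invites, informs and takes consent; stress test; research team enrols those still eligible and hands over the envelope; participant opens it. The code is made at some point before the handover. Opening the envelope reveals the arm, so its content is the allocation and not merely an identifier.

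**2. Who can know the arm before the envelope is opened.**

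| Person | Could know the arm beforehand? | Basis |
|---|---|---|
| Participant | No | Opaque envelope, opened after enrolment |
| Recruiting family doctor | No, on the procedure described | Not given a role in generation |
| Enrolling staff who did not generate the codes | No, if the envelope is intact and the list is not shared | Opaque envelope |
| Principal investigator | Yes | Generates the codes |

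The principal investigator belongs to the team that enrols, so the last row is the gap.

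**3. When the code is made.** Two readings fit the text.

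- *Before the stress-test result.* The list-maker could know the arm while eligibility itself is open. This sits badly with Design, which randomizes men who are already eligible.
- *After eligibility is confirmed, but before handover.* This agrees with Design. The exposed window is shorter, covering enrolment only, but generation and enrolment are still in the same hands.

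The role overlap exists on both readings; only the length of the window changes. The two sections need to be reconciled.

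**4. Side check: is power at stake if the arms come out unequal?** Inputs from Data Analysis and Sample Size: 162 evaluable, difference 0.35, power 80%, significance 5% (two-sided assumed), follow-up 80%, 200 enrolled. The SD is not given, so it is solved backwards:

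SD = 0.35 × √(81/2) / (1.960 + 0.842) = 0.35 × 6.364 / 2.802 = 0.795.

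This returns the stated 162 by construction and does not test it independently. Power = Φ(0.35 / SE − 1.960), with SE = 0.795 × √(1/n₁ + 1/n₂):

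- 100:100 enrolled, 80:80 analysed: SE = 0.1257, power = 79.5%.
- 114:86 enrolled, 91.2:68.8 analysed: SE = 0.1270, power = 78.7%.

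The second split is about two standard deviations from even under unrestricted randomisation of 200 men (SD = √(200 × 0.25) = 7.07). The loss is under one percentage point, so what is at stake is selection, not power.

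**The case against.** The strongest reply is that ordinary safeguards are present. The envelope is opaque, is handed over only after the stress test, and is opened by the participant himself. A list made in advance and released after eligibility is normal practice. The article does not say who judges the stress test, nor who keeps the list once it is made, so a route from knowledge to selective entry has to be supposed. Sealing, numbering and blocking may well be in the full protocol, and a condensed article need not give them.

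Much of this stands: concealment is partial rather than absent, and missing blocking or numbering detail is no finding. What remains is the procedure the article does state. The person who generates the codes sits on the team that enrols. Even if the wording about each participant is read loosely as a prepared sequence, its author would know the next entry.

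Three stronger readings are tempting but not supported.

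- **The code is fixed for a named man before the stress-test decision.** The text dates the code only before handover, speaks of participants rather than named men, and is offset by the Design section.
- **An even split within each unit is planned and will fail.** A 20:20 split is derived from 1:1 allocation and an expected 40 men per unit; it is not stated. Probabilities of missing it would assume unrestricted randomisation, which the article does not assert.
- **Uneven units would conflict with the playing groups.** The article says "The participants will be organized into 5 groups of 20 players in different time schedules" but does not tie those groups to the units.

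**Conclusion.** The concern holds in a limited form. The article assigns generation of the allocation to a member of the unblinded team that enrols, attaches the code to a participant before he is enrolled, and leaves unclear whether the code precedes confirmed eligibility. One person, or anyone with whom the list is shared, can know a man's arm while his entry is being settled.

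The conclusion rests on two readings: that the principal investigator, as a team member, is not kept apart from enrolment (no separation is stated), and that the code in the envelope is the allocation.

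The size of any bias cannot be derived. It depends on how often knowledge of the arm would change an entry decision and on how different those men would be, and the article gives neither. A figure would be invention. The article does not show that selection will occur, only that the described procedure does not prevent it. It should be corrected before recruitment.

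**What to change.** Reword Assignment of Interventions so that:

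1. an existing team member who neither enrols nor assesses participants generates and holds the list, and the principal investigator has no access to it during recruitment;
2. the list is 1:1, stratified by primary health care unit, with varied block sizes that are not disclosed to enrolling staff (in an unblinded trial, fixed or known blocks would let staff predict later allocations);
3. each code belongs to the next sequentially numbered, sealed, opaque envelope for that unit, not to a person;
4. the envelope is released only after the stress test is passed and the man is logged as enrolled, which also brings the section into line with Design.

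The cost is small. A task moves to someone already on the team, one paragraph is rewritten, and envelopes need a custodian and a log. The Results section says that ethics submission is still being prepared and that recruitment will follow approval, so the change can be made before any man is allocated. Sample size and analysis do not need to change for this point.

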### Data Collection

Data collection will have 3 main time points: baseline (before starting the study), 6 months (after the study ends), and every walking football exercise session. The descriptions of the variables assessed at baseline and the 6-month evaluation are presented in Table 1.

**Table 1 table1:** Variables assessed at baseline and at the end of the study.

Variable		Method
**Glycemic control**		
	Glycated hemoglobin	Venous blood analysis
	Fasting blood glucose	Venous blood analysis
**Blood lipid profile**		
	Total cholesterol	Venous blood analysis
	LDL^a^ cholesterol	Venous blood analysis
	HDL^b^ cholesterol	Venous blood analysis
	Triglycerides	Venous blood analysis
**Blood pressure**		
	Systolic blood pressure	Automatic digital sphygmomanometer
	Diastolic blood pressure	Automatic digital sphygmomanometer
**Anthropometric profile**		
	Body mass index	Formula
	Waist circumference	Anthropometric tape
**Body composition**		
	Fat mass	Bioelectrical impedance analysis
	Fat-free mass	Bioelectrical impedance analysis
Habitual physical activity		Global Physical Activity Questionnaire score [26]
Dietary intake		3-day food record, 24-hour dietary recall analysis
Health-related quality of life		EQ-5D questionnaire [27]
Medication (number, type, and dosage)		Form

^a^LDL: low-density lipoprotein.

^b^HDL: high-density lipoprotein.

Before and after the study, habitual physical activity, dietary intake, health-related quality of life, and regular medication will be collected to be used as control variables. We will also collect sociodemographic characteristics at baseline.

At every exercise session, objective and subjective exercise intensity and enjoyment will be recorded for control purposes.

The descriptions of the variables to be assessed before, during, and after each exercise session are detailed in Table 2. Capillary blood glucose, blood pressure, and feet wounds will be assessed before the exercise session; objective exercise intensity will be recorded during the exercise session; subjective exercise intensity and enjoyment will be assessed at the end of the exercise session; and exercise-related injuries and adverse events will be evaluated during and after the exercise session if participants report symptoms or the nurse notices any issue.

**Table 2 table2:** Variables assessed in each exercise session.

Variable		Method
Pre-exercise capillary blood glucose		Glucometer
Pre-exercise blood pressure		Automatic digital sphygmomanometer
Pre-exercise feet wounds		Self-observation
**Exercise intensity**		
	Subjective	OMNI perceived exertion scale [28]
	Objective	Heart rate and time-motion tracking
Exercise sessions enjoyment		Physical Activity Enjoyment Scale [29]
Exercise-related injuries and adverse events		Observational/clinical/self-reported

All personnel involved in the study — nurses, nutritionists, medical doctors, football coaches, and sports scientists — will receive training before baseline assessments. This aims to standardize procedures.

Specifically, the principal investigator will provide training to the other research team members regarding the clinical assessments and forms.

The Portugal Football School of the Portuguese Football Federation will provide training to football coaches to ensure the walking football program is administered in a similar way in the different centers and according to a predefined manual.

A sports scientist will monitor, in real time, internal (heart rate [HR]) and external (eg, distance covered, number of actions) workload and apply the OMNI perceived exertion scale in all sessions.

The nurse must have training in emergency procedures, be responsible for measurements at exercise sessions, manage and record exercise-related injuries and adverse events, follow-up with participants, and refer to health care facilities if necessary.

### Procedures

Before each walking football session, the nurse present at the local sports facility will evaluate capillary blood glucose (Contour XT, Ascencia Diabetes Care, Basel, Switzerland) and blood pressure (M6 Comfort, Omron, Kyoto, Japan) for all participants. Furthermore, participants will self-observe the presence of feet wounds and report any to the nurse. These measurements aim to evaluate the baseline safety conditions before the exercise session.

The participants will be allowed to start the session only under the following conditions: (1) capillary blood glucose ≥100 and ≤300 mg/dL, (2) systolic blood pressure ≤200 mm Hg, (3) diastolic blood pressure ≤100 mm Hg, and (4) no foot wounds.

During and after sessions, capillary blood glucose, blood pressure, and feet will be evaluated if participants report related symptoms. An adverse event is considered if there are any of the following after reporting symptoms: capillary blood glucose <72 mg/dL (symptomatic hypoglycemia) or >300 mg/dL (symptomatic hyperglycemia), systolic blood pressure <100 mm Hg (symptomatic hypotension) or >160 mm Hg (symptomatic hypertension response), or foot wounds are observed [3,23]. Participants in these conditions will not return to the exercise session, and corrective measures will be applied when necessary (ie, hydration, glucose intake, rest).

Strains, sprains, and contusions will be considered musculoskeletal injuries. Falls, seizures, myalgias, headache, malaise, chest pain and discomfort, and other relevant events will be considered adverse events [22].

During the walking football program, exercise intensity will be monitored systematically in every session through HR and rating of perceived exertion (RPE). From the estimated HR reserve (HRR) [30], we will classify the exercise intensity using the method by Karvonen and Vuorimaa [31]: light intensity (30%-39% HRR), moderate intensity (40%-59% HRR), vigorous intensity (60%-89% HRR), and near-maximal to maximal intensity (≥90% HHR) [32]. During training sessions, all participants will use adjustable chest strap HR monitors, and HR will be recorded at 5-second intervals using short-range radio telemetry (Firstbeat Sports, Jyväskylä, Finland). Participants will classify subjective exercise intensity through RPE using the 11-point OMNI scale (from extremely easy [0 points] to extremely hard [10 points]) at the end of the session [28]. With this RPE scale, light intensity is considered as 3-4 points, moderate intensity as 5-6 points, vigorous intensity as 7-8 points, and near-maximal to maximal intensity as 9-10 points.

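### The systolic range allowed at the start of a session overlaps the systolic adverse-event range, so pressure that has not changed, or has improved, can be labelled a response to exercise

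*Protocol article*

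**What the plan says.** All of the rules are in the Methods of the protocol article.

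- **Start rule (Procedures).** Besides a glucose window, a session may begin only if these hold: "2) systolic blood pressure ≤200 mm Hg, (3) diastolic blood pressure ≤100 mm Hg, and (4) no foot wounds". No lower systolic limit is given.
- **Pre-session measurement (Data Collection, text after Table 1).** "Capillary blood glucose, blood pressure, and feet wounds will be assessed before the exercise session". Procedures gives the purpose: "These measurements aim to evaluate the baseline safety conditions before the exercise session".
- **When pressure is measured again (Procedures).** "During and after sessions, capillary blood glucose, blood pressure, and feet will be evaluated if participants report related symptoms".
- **Event rule (Procedures).** "An adverse event is considered if there are any of the following after reporting symptoms"; the systolic items are "systolic blood pressure <100 mm Hg (symptomatic hypotension) or >160 mm Hg (symptomatic hypertension response". The rule does not mention the pre-session value.
- **Symptoms in their own right (Procedures, last paragraph).** Headache, malaise, chest pain and several other complaints are adverse events whatever the blood pressure.
- **Use of the count (Outcomes).** "Secondary outcomes also include the incidence of exercise-related injuries and adverse events".

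**The concern.** The high-pressure event is named as a response, and the outcome is described as exercise-related. Both imply that something changed because of the session. The definition, however, is a fixed value, and the start rule admits men who are already past that value. For them the label carries no information about what the session did.

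At stake is how the haemodynamic part of the safety outcome can be read. The article describes these events as recorded at exercise sessions, which only the intervention group attends. It describes no matching count in the control group that would show how often raised pressure and a symptom coincide without exercise. Attribution to exercise therefore rests on the event definition. The Discussion expects a low rate of such events, and part of the rate would reflect how many men arrive with high (or low) pressure.

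**Working it through.** The article gives no figure to reproduce, so the check sets the start rule beside the event rule for each measured criterion that has a numerical or yes/no event limit (all from Procedures).

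| Criterion | Allowed at start | Event after symptoms | Overlap |
|---|---|---|---|
| Systolic pressure, high side | up to 200 mm Hg | above 160 | 161 to 200 (40 whole-number values) |
| Systolic pressure, low side | no limit | below 100 | every value below 100 |
| Capillary glucose | 100 to 300 mg/dL | below 72 or above 300 | none |
| Foot wounds | none allowed | wound observed | none |

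For glucose and foot wounds, an event means that the man's state has changed since the start check. Systolic pressure is the only criterion in the table for which the event limit can be met before exercise begins.

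**What the rule does with individual men (illustrative values):**

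- Start 175, related symptom, then 165: change 165 − 175 = −10 mm Hg. Recorded as a hypertension response.
- Start 98, related symptom, then 98: change 0. Recorded as hypotension.
- Start 165, related symptom, then 215: change 215 − 165 = +50 mm Hg. Recorded as a hypertension response, the same label as the first man.

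The rule cannot tell the first man from the third, although the reading that separates them has been taken.

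**How many sessions could be exposed.** The documents give no distribution of pre-session systolic pressure, so the following is an assumption, shown as a range. Full attendance gives 5 groups × 20 men × 72 sessions = 7,200 man-sessions. The share starting at 161 to 200 is taken as Φ((200.5 − m)/s) − Φ((160.5 − m)/s) for a normal distribution with mean m and SD s.

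| Assumed mean (SD), mm Hg | Share at 161–200 | Man-sessions of 7,200 |
|---|---|---|
| 130 (14) | 1.5% | 106 |
| 135 (15) | 4.5% | 321 |
| 138 (16) | 8.0% | 574 |
| 142 (17) | 13.8% | 993 |
| 145 (18) | 19.4% | 1,394 |

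Under the same assumptions, 0.6% to 1.5% start below 100. These are sessions in which the label could go wrong. They are not wrong labels: an event also needs a related symptom, and the documents give no symptom rate. The figures also ignore the diastolic start limit, which bars some of the same men, as well as screening at the stress test and missed sessions.

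**The case against.** The case against has real force on several points.

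- **A reader might infer that each such case is a false event.** The text does not support that in general. A man whose related symptom is headache or malaise is already an adverse event under the last paragraph of Procedures. For him the systolic rule gives the wrong label or a second entry. An additional event can arise only from a related symptom that does not itself count.
- **A reader might infer that any complaint triggers the rule, or that hundreds of false events follow.** Pressure is remeasured only for related symptoms, and the man-session figures above measure exposure under assumed distributions.
- **A reader might infer that the whole safety outcome is unreadable.** It is not. Injuries, falls, glucose events and foot wounds are untouched.
- **Direction.** The flaw adds to recorded harm, so it works against the expected low rate and does not give false reassurance. This lowers the weight of the point, but a wrong attribution remains wrong.
- **Two limits may serve two purposes.** One decides who may start; the other labels a man with symptoms. The event limits are attributed to cited sources that are not at hand. Different limits are not in themselves an error. The fault is that the event is called a response while the start state is ignored.
- **The pre-session data exist, so an analysis plan could split the events.** True, and this makes the repair cheap. But the article itself fixes the definition, and that definition is what produces the label.
- **An obvious repair would do harm.** Counting only events that crossed the limit from a reading inside it would drop the man who rises from 165 to 215. That objection is accepted, and the fix below avoids it.

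**Conclusion.** The point holds in a limited form. The systolic start and event ranges overlap at 161 to 200 mm Hg and below 100 mm Hg. The event definition makes no use of the recorded pre-session value, so an unchanged or improved reading after a related symptom is labelled an exercise response. This follows from the text alone and needs no assumption.

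The consequence is confined to the haemodynamic category of a secondary safety outcome: wrong labels or double entries for symptoms that already count, and possible extra events for other related symptoms. The number affected cannot be calculated, because neither the distribution of pre-session pressure nor the symptom rate is given. The primary comparison of glycated haemoglobin is unaffected.

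**What to change.** 1. **Reconcile the limits.** The investigators should bring the systolic start limit and the systolic event limits in Procedures into agreement, or state why they differ. Which values are right is a clinical matter on which this review takes no view.
2. **Keep every symptomatic systolic event in the count, and split the report.** Show separately the events in which the pre-session reading was inside the event limits and those in which it was already outside, each with the change from the pre-session reading. A further rise in a man who started high is then still shown as a response (165 to 215), while an unchanged or falling reading is not (175 to 165). Treat the low side in the same way.
3. **Count each episode once.** Where the symptom is already an adverse event, record the systolic reading as a feature of that episode and not as a second event.

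The cost is a sentence or two in Procedures, one derived variable and a split table line. No new measurement is needed and no event is lost. The Results section says that recruitment will start only after ethics approval, so the rule can be set before any data exist.
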